### 4.4. Sample Size

Per Morin-Papunen et al., 2003, the most prominent serum metabolite testosterone decreased by 2.7 ± 0.3 to 2.0 ± 0.2 nmol/liter in patients receiving metformin (500 mg twice daily for 3 months or longer, then 1000 mg twice daily for 3 months or longer) [61]. By taking an alpha of 0.05% corrected by Bonferonni (0.005/44 (number of metabolites intended to analyze) = 0.001136) and a target power of 80% we would get an n = 7 patients [62]. However, this must be taken with a grain of salt as a very optimistic assumption for our purposes. We suggest that for not yet measured and reported effects on metabolites such as, e.g., androsterone, eticholanolone, dehydroepiandrosterone, epitestosterone effect sizes are much lower in the range of one-fourth of the above-mentioned testosterone. Therefore, the number needed to analyze will be around 45 patients. This estimate would be further supported by analyses by Baillargeon et al., 2004 [42], Chou et al., 2003 [46], Cibula et al., 2005 [47], Gambineri et al., 2006 [48], Ibanez et al., 2004 [49], Nestler et al., 1997 [41] and Tang et al., 2006 [50] analyzing effects of metformin mainly on androgen and estrogen markers. Furthermore, the proposed number of 45 would also potentially allow us to find an effect on steroid hormone profiles at lower dosages than described by Morin-Papunen [61]. Concerning the Autism questionnaire, it is to mention that an average score in students of 17.6 ± 6.4 was detected compared to healthy controls with an average score of 16.4 ± 6.3, yielding an alpha of 0.05% and a target power of 80% to a large sample size of 894 subjects [53]. When performing a comparison with students participating in the Math Olympiad scoring 24.5 ± 6.4 versus students with the already mentioned score of 17.6 ± 6.4, a sample size of 28 results [53]. These findings do not differ largely when it is stratified for sex, despite the fact that women tend to score lower [38]. To summarize, if there is a substantial effect of metformin, the proposed sample size of around 45 will be sufficient to detect differences.

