### 3.6. Recruitment

As the detailed sample size calculation (see Section 4.4) already indicates to have an effect with a small sample size of seven persons, the aim is in consequence to gain 10 female and male patients of approximately the same age for the study estimate to conduct first rough analyses.

Further, based on the number of patients per year in our clinical setting, it seems reasonable to win enough patients within 2 years. We estimate an average of one patient a week, yielding a total of 50 patients a year so that we will have enrolled a total of around 100 patients after 2 years. The recruitment will be conducted by the department of internal medicine of the Lindenhofgruppe and its associated General practitioners. Due to the common characteristics of patients with type 2 diabetes mellitus we expect to mainly recruit patients above 50 years of age and slightly more male than female patients. Furthermore, the obstetrics department of Inselspital Berne with its Patients with a potential indication of metformin due to PCOS will also be included.

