## 4. Data Collection Methods

### 4.1. Steroid Measurement Procedures

Analysis of urinary steroids will be conducted via gas chromatography–mass spectrometry. Urine samples shall be taken prior to treatment start and after 12 weeks of treatment (gold standard: 15 mL from a 24 h urine collection). Urine sample preparation comprises pre-extraction, enzymatic hydrolysis, extraction from the hydrolysis mixture, derivatization and gel filtration. The recovery standard will be prepared by adding 2.5 µg of medroxyprogesterone to 1.5 mL of urine. The sample will be extracted on a Sep-Pak C18 column (Waters Corp., Milford, MA, USA), dried, reconstituted in a 0.1 M acetate buffer, pH 4.6, and hydrolyzed with a powdered Helix pomatia enzyme (12.5 mg; Sigma Chemical Co., St. Louis, MI, USA) and 12.5 µL of β-glucuronidase/arylsulfatase liquid enzyme (Roche Diagnostics, Rotkreuz, Switzerland). The resulting free steroids will be extracted on a Sep-Pak C18 cartridge. A mixture of internal standards (2.5 µg each of 5α-androstane-3α, 17α-diol, stigmasterol, and cholesterol butyrate, and 0.15 µg of 3β5β-tetrahydroaldosterone) will be added to this extract, and the sample will be derivatized to form the methyloxime-trimethylsilylethers. Analyses will be performed on a Hewlett Packard gas chromatograph 6890 (Hewlett Packard, Palo Alto, CA, USA) with a mass selective detector 5973 by selective ion monitoring (SIM). One characteristic ion will be chosen for each compound measured. The derivatized samples will be analyzed during a temperature-programmed run (210–265 °C) over a 35 min period. The calibration standard consists of a steroid mixture containing known quantities of all the steroid metabolites to be measured. Responses and retention times will be recorded regularly. In each case, the ion peak will be quantified against the internal stigmasterol standard. All procedures will be performed as described several times by us and others [16,18,58,59,60].

The following metabolites shall be measured as described above [15,16]:

Androgen metabolites: Androsterone, Etiocholanolone, Androstenediol, 11-Oxoetiocholanolone, 11β-Hydroxyandrosterone, 11β-Hydroxyetiocholanolone, Dehydroepiandrosterone, 5-Androstene-3β,17β-diol, 16α-Hydroxydehydroepiandrosterone, 5-Androstene-3β,16α,17β-triol, 5-Pregnene-3β, 16α,17β-triol, Testosterone, 5α-Dihydrotestosterone

Estrogen metabolites: Estriol, 17b-Estradiol.

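### Section 4.4 misprints the per-metabolite significance threshold and its divisor does not match the metabolite list; 45 patients remain adequate at the alpha actually used, but only under an unstated SD and correlation assumption

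*Protocol article*

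**What the plan says.** The primary endpoint is the change in urinary steroid profiles from before metformin to 12 weeks. Section 5 tests each metabolite with a two-sided paired t-test (Wilcoxon if not normal) under a Bonferroni correction. It gives neither the overall alpha nor the number of tests. Both appear only in Section 4.4, which gives the overall alpha and the correction together: "By taking an alpha of 0.05% corrected by Bonferonni (0.005/44 (number of metabolites intended to analyze) = 0.001136".

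The effect comes from a published study in which serum "testosterone decreased by 2.7 ± 0.3 to 2.0 ± 0.2 nmol/liter". From this, 4.4 says that with "a target power of 80% we would get an n = 7 patients". It then assumes one-fourth of that effect for metabolites not yet studied: "Therefore, the number needed to analyze will be around 45 patients". The questionnaire calculations in the same section repeat the 0.05% and give 894 and 28 subjects.

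Section 4.1 lists the metabolites to be measured by class. On enrolment, Section 3.6 expects that "we will have enrolled a total of around 100 patients after 2 years".

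**The concern.** One sentence carries three overall alphas: 0.05% (0.0005), 0.005, and the 0.05 implied by the printed quotient. They span a hundredfold. The divisor is tied to a metabolite count that the document's own list does not support. Because Section 5 leaves alpha and family size open, 4.4 is the only place in this document that fixes the decision rule for the primary endpoint. As written, a reader must work back from the sample sizes to learn which threshold applies, and the family size (39 or 44) is unsettled before data are seen. The stated 80% power also needs checking, since it depends on the alpha and on how the ± values were used.

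**Working it through.** **1. The quotient.**
- 0.05/44 = 0.001136 (the printed result)
- 0.005/44 = 0.000114 (the printed formula)
- 0.0005/44 = 0.0000114 (the printed 0.05%)
- 0.05/39 = 0.001282

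**2. The metabolite count in Section 4.1.** Androgen 13 + estrogen 2 + progesterone 4 + aldosterone 1 + corticosterone 6 + cortisone 5 + cortisol 8 = 39. Epitestosterone, a target in 4.4, is not among them.

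**3. Reproducing 7 and 45.** Inputs from 4.4: change 2.7 − 2.0 = 0.7, with ± 0.3 and ± 0.2 read as SDs (assumption). Test from Section 5: two-sided paired t, computed with the exact noncentral t. Two ways to standardise:
- SD of the difference = √(0.3² + 0.2² − 2r × 0.3 × 0.2) = √(0.13 − 0.12r). With r = 0.5 (assumption) this is 0.265, so dz = 0.7/0.265 = 2.65, and one-fourth is 0.661.
- Pooled SD = √((0.09 + 0.04)/2) = 0.255, so d = 2.75, and one-fourth is 0.686.

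| Per-test alpha | n, full effect (r = 0.5 / pooled) | n, one-fourth effect | Power with 45 pairs, one-fourth effect |
|---|---|---|---|
| 0.05/44 | 8 / 7 | 44 / 41 | 82.0% / 85.8% |
| 0.05/39 | 8 / 7 | 43 / 41 | 83.0% / 86.7% |
| 0.005/44 | 10 / 10 | 58 / 55 | 58.1% / 64.0% |
| 0.0005/44 | 12 / 12 | 72 / 68 | 33.4% / 39.0% |

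Only the first two rows come close to the stated 7 and 45. At 0.005/44, seven patients would give just 30–34% power at the full effect.

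**4. Cross-check on the 0.05% notation.** The questionnaire figures follow from n per group = 2 × ((z₁ + z₂) × SD/difference)², with SD 6.4.
- Two-sided alpha 0.05, 80% power: z sum = 2.80. Difference 17.6 − 16.4 = 1.2 gives 446.5, rounded up to 447, and 2 × 447 = 894. Difference 24.5 − 17.6 = 6.9 gives 13.5, rounded up to 14, and 2 × 14 = 28. Both match exactly.
- Two-sided alpha 0.0005: z sum = 4.32. The results would be 2 × 1063 = 2126 and 2 × 33 = 66.

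So 0.05% is a misprint for 0.05 in both places.

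**5. Sensitivity to the unstated correlation**, at 0.05/44 and the one-fourth effect:

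| r | dz | Pairs needed for 80% | Power with 45 pairs |
|---|---|---|---|
| 0 | 0.485 | 77 | 42% |
| 0.3 | 0.571 | 57 | 64% |
| 0.5 | 0.661 | 44 | 82% |
| 0.7 | 0.816 | 31 | 97% |

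**The case against.** A reader might infer that the wrong arithmetic leaves 45 patients underpowered, or that an analyst would apply a threshold ten times too strict. The documents do not support either. The printed result, 0.001136, is the correct value of 0.05/44 and stands beside the faulty formula; at that level 45 pairs exceed 80% under the assumptions above. The 58–64% and 33–39% figures describe calculations that the plan's own 7, 45, 894 and 28 rule out. The count mismatch cannot cause a shortfall either, since dividing by 39 loosens the threshold and slightly raises power.

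Nor do 45 and about 100 conflict: the first is the number to be analysed, the second a forecast of two-year enrolment, and the gap between them leaves room for lost pairs. The test and its sidedness are stated in Section 5, and the pooled SD named there for effect sizes gives 7 and 41 without any correlation.

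It is also fair to say that a condensed article may leave a correlation assumption to the full protocol, and that the authors call the n = 7 calculation very optimistic and cut the effect to one-fourth.

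What survives is that the text contradicts itself on the primary-endpoint threshold and on the family size. It also concludes that around 45 suffices, conditional only on a substantial effect, when that depends equally on how variable the paired differences are.

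**Conclusion.** The point holds as an error in the written threshold. The formula is wrong by a factor of 10, the percentage by a factor of 100, and the divisor disagrees with the list by 5 metabolites. The choice between 39 and 44 moves the per-test level only from 0.00114 to 0.00128 and power by about one percentage point.

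The sample size stands for this purpose: about 82–86% power with 45 evaluable pairs at 0.05/44, if the ± values are SDs and r is about 0.5 or the pooled SD is used. Those conditions matter more than the misprint, as power ranges from 42% to 97% over r = 0 to 0.7. The ± values are unlabelled. Were they standard errors from a group of 8–20 (an assumption; the document gives no group size), power at 45 would be below 5% for r between 0 and 0.5. Nothing in the document shows that they are standard errors, so this is a reason to label them and not a finding that the trial is underpowered.

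**What to change.** In Section 4.4:
- Replace 0.05% with a two-sided family-wise alpha of 5% in both places, and correct the numerator to 0.05.
- Settle the family size before analysis: either 0.05/39 = 0.00128 for the metabolites listed in 4.1, or add the missing ones (including epitestosterone, if it is to be measured) and keep 0.05/44 = 0.00114. Use the same number in Section 5.
- Say whether ± 0.3 and ± 0.2 are SDs, and recompute if they are not.
- State the assumed pre/post correlation, or that the pooled SD was used, and qualify the 80% power at 45 evaluable pairs accordingly (at 0.05/44: about 42% at r = 0, 64% at r = 0.3, 82% at r = 0.5).

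The cost is wording only. No change to N, to the test or to data collection is needed; the stated power becomes a conditional and less favourable range.

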For this purpose, we want to analyze the change in social behavior and steroid hormone profiles, as well as their potential correlation, under metformin treatment. Because only urinary metabolites of steroid hormones and not the blood serum levels themselves will be examined, there is a certain limitation concerning the reliability of measured outcomes; also, comparisons with other studies might be restricted. We chose this measurement because of its general availability and ease of use for both patient and physician to ensure easier recruitment and follow-up. As a general research question, we suspect that certain substances modulate social behavior via steroid hormones, which act as an intermediary in social behavior. Therefore, we will measure both urinary steroid hormone profiles as well as social behavior through an Autism Spectrum Quotient respectively questionnaire before treatment start and after.

Although we expect our patient sample of adults not typically affected by social behavioral disorders or autism spectrum disorders to score in the lower spectrum of the questionnaire, we have chosen this tool because of its simplicity in use to ensure sufficient patient recruitment and follow-up. The questionnaire has been tested in both adults with autism spectrum diseases as well as healthy adults. In healthy adults, significant differences between genders and different backgrounds (mathematics vs. humanities) were recorded, while all scores remained in the lower spectrum [53]. As discussed above, we expect social behavioral changes to impact foremost social withdrawal and anxiety, traits that are well covered in the AQ. Thus, we hope to record significant changes even in healthy adults. Furthermore, we already showed an effect in our own mouse model while also using a strong simplification of social behavioral measurement [19]. Yet, the simple way to assess social behavior remains one limitation; more proven and elaborative possibilities might be used, especially in studies explicitly focused on specific pharmaceutical targets and their involvement in social behavior.

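### The AQ sample sizes of 894 and 28 are two-independent-group totals at 5% from between-population contrasts; they do not fit the one-group before-after design, and the effect for which about 45 is said to suffice is undefined

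*Protocol article*

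**What the plan says.** Section 4.4 takes two AQ contrasts from a cited study. The first is between students and controls: "an average score in students of 17.6 ± 6.4 was detected compared to healthy controls with an average score of 16.4 ± 6.3". From this it reports "yielding an alpha of 0.05% and a target power of 80% to a large sample size of 894 subjects". The second is between "students participating in the Math Olympiad scoring 24.5 ± 6.4 versus students with the already mentioned score of 17.6 ± 6.4", for which "a sample size of 28 results". The section then concludes: "To summarize, if there is a substantial effect of metformin, the proposed sample size of around 45 will be sufficient to detect differences".

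The AQ endpoint in Section 3.3.2 is the change in each patient from before metformin to 12 weeks. Section 3.1 describes one cohort with a baseline and a 12-week assessment. Section 5 names two-tailed dependent t-tests for the pre-post comparison of metabolites. Section 6 adds that "we expect our patient sample of adults not typically affected by social behavioral disorders or autism spectrum disorders to score in the lower spectrum". The article gives no SD of within-patient AQ change, no pre-post correlation and no expected AQ change under metformin.

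**The concern.** Three things do not fit together.

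- **Design.** Both contrasts compare different people at one time. A change within the same people over 12 weeks has a different variance, which depends on how strongly the two scores correlate.
- **Benchmark.** The only AQ figure below 45 rests on a gap of 6.9 points, or 6.9/6.4 = 1.08 SD, between mathematics contestants and other students. Nothing in the article links a gap of that size to metformin, and the patients are expected to score low.
- **Conclusion.** The two AQ figures lie far on either side of 45. The 45 itself comes from the steroid calculation earlier in Section 4.4.

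At stake is how the secondary AQ result can be read. With no stated detectable change, a reader cannot tell which effects a non-significant result would leave open.

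**Working it through.** **Inputs.** Section 4.4 gives the differences 17.6 − 16.4 = 1.2 and 24.5 − 17.6 = 6.9, SD 6.4 (6.3 in controls), 80% power, alpha printed as 0.05%, and the planned 45. Section 5 gives two-sided paired testing; it states this for metabolites, and I assume the same for the AQ. The pre-post correlation r is not in the article, so I assume a range.

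**Step 1: reproduce the printed figures.** For two independent groups with the normal approximation, n per group = 2(z₁₋α/₂ + z₀.₈)² SD²/δ². At two-sided 5% the squared term is 7.849.

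- δ = 1.2: 2 × 7.849 × 6.4²/1.2² = 446.5, so 447 per group and **894** in total.
- δ = 6.9: 2 × 7.849 × 6.4²/6.9² = 13.5, so 14 per group and **28** in total.

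Both match exactly. At the printed 0.05% (0.0005) the formula gives 1,063 and 33 per group, totals of 2,126 and 66, which do not match. One-sided 5% gives 704 and 22, which do not match either.

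**Step 2: the same differences in the trial's own design.** With equal SD at both visits, SD of change = 6.4 × √(2(1 − r)). Sample size and power come from the noncentral t distribution at two-sided 5%.

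| Assumed r | SD of change | Pairs for 1.2 points | Power of 45 pairs for 1.2 points | Pairs for 6.9 points | Change detectable with 45 pairs, 80% power |
|---|---|---|---|---|---|
| 0 | 9.05 | 449 | 14% | 16 | 3.9 |
| 0.5 | 6.40 | 226 | 23% | 9 | 2.7 |
| 0.7 | 4.96 | 136 | 36% | 7 | 2.1 |
| 0.8 | 4.05 | 92 | 49% | 5 | 1.7 |
| 0.9 | 2.86 | 47 | 79% | 4 | 1.2 |

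The last column is 0.427 × SD of change, where 0.427 is the standardised change that 45 pairs detect with 80% power. For example, 0.427 × 6.40 = 2.7.

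**Step 3: threshold.** For 1.2 points, 45 pairs reach 80% power only when r is about 0.90 or higher. For 6.9 points, power with 45 pairs is above 99% at every r shown.

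**The case against.** The closing sentence is conditional. A reader might infer that the protocol ignores its own 894, or that 45 is too few for the AQ. The text supports neither. It reports 894, calls it large, and then restricts the conclusion to a substantial effect. If that means the 6.9-point gap, 45 pairs are more than enough: at most 16 are needed at 5%, and at most 39 even at 0.05%. The design error is then on the safe side.

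A reader might also infer that 45 pairs simply cannot detect 1.2 points. That depends on r, which the article does not give; at r = 0.9 power is 79%. Section 3.6 also expects around 100 patients enrolled, which would cover 1.2 points at r = 0.8 (92 needed), though not at r = 0.7 (136 needed).

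The alpha is very probably a notation slip. The same 0.05% precedes the steroid calculation, where the printed 0.001136 equals 0.05/44. The AQ is a secondary endpoint in a study that Section 7.1 calls exploratory, and no section says that a null AQ result would be taken as proof of no effect.

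All of this stands as a limit on the point. It does not rescue the two figures, which are for another design, and it does not supply the missing definition. Without a stated size, the condition cannot be checked against any result.

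**Conclusion.** The point holds in a limited form. The figures 894 and 28 are exact totals for two independent groups at two-sided 5% and do not apply to a one-group before-after comparison; the printed alpha contradicts them. This part needs no assumption about r.

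Whether about 45 suffices cannot be judged as written, because the effect it refers to is undefined. The protocol's own two differences give opposite answers: ample for 6.9 points, and 14% to 79% power for 1.2 points over r from 0 to 0.9. These paired figures assume that an SD of 6.4, taken from students, holds at both visits in the trial's patients, and that all 45 pairs are evaluable.

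What is shown is that the AQ justification is missing, not that the trial is too small. Because the AQ is secondary and did not set the 45, this is a correction that should be made rather than a bar to the study.

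**What to change.** In Section 4.4:

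1. Correct alpha for the AQ to 5%.
2. Replace 894 and 28 with the detectable within-patient change. Possible text: *With 45 evaluable pairs, two-sided alpha of 5% and 80% power, the detectable mean AQ change is 3.9, 2.7, 2.1, 1.7 or 1.2 points if the pre-post correlation is 0, 0.5, 0.7, 0.8 or 0.9. The SD of 6.4 at each visit (from a student sample) and the correlation are assumptions.* If the sponsor has a sourced SD of change for a comparable population, use it instead.
3. Limit the closing sufficiency sentence to AQ changes of at least that size.
4. Commit to reporting the mean AQ change with its 95% confidence interval, so that readers can see which changes the data leave open.

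The cost is protocol wording and a more modest AQ claim. Recruitment and procedures need not change.

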## 5. Statistical Analysis

Mean and SEM (standard error of mean) of all metabolites will be calculated pre-versus post intervention for the respective sub-samples distinguished by age and sex. To analyze the distribution patterns of the measured values of each metabolite Kolmogorov–Smirnov tests will be conducted. If normality distribution is present, the differences between pre-versus post intervention shall be analyzed with two-tailed dependent t-tests while correcting for multiple comparisons with Bonferroni correction. If the hypothesis of normal distribution must be rejected for metabolite concentrations pre-versus post intervention, Wilcoxon tests shall be conducted. If normal distribution is present, differences pre-versus post intervention will be further quantified with the calculation of effect sizes by Cohen with pooled standard deviation and 95% confidence intervals [63,64]. For metabolites not showing a normal distribution, effect sizes shall be calculated according to Pallant (2005) [65,66]. Correlation analysis (Pearson correlation coefficient) will be conducted to detect a potential relationship between cumulative metformin dosage (standardized for body weight and treatment duration] and steroid hormone concentrations, respectively, scores from the autism questionnaire. For female subjects before versus after menopause, analyses will be conducted separately. Potential differences will be compared with prior gained reference values from our lab [67]. As we do have a pool of healthy subjects, an individually pairwise matched design (twin matching) might be another possibility to reduce an age bias increasing the validity of the results [67].

Based on these preliminary analyses, structure equation modeling can be applied if indicated in order to combine findings from biochemical analysis and from questionnaires. All calculations will be performed with GraphPad Prism (GraphPad Software, Inc., La Jolla, CA, USA) and SPSS (Microsoft Inc., Redmond, WA, USA).

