### 3.3. Endpoints

#### 3.3.1. Primary Research Endpoint

Changes in steroid hormone profiles of interest (see below) prior to metformin treatment start and after 12 weeks of treatment.

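### Section 5 summarises every metabolite by mean and SEM at each visit, which suits neither the within-patient endpoint nor skewed metabolites (low-severity reporting fix)

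*Protocol article*

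**What the plan says.** Section 3.3.1 of the protocol article defines the primary endpoint as a change: "Changes in steroid hormone profiles of interest (see below) prior to metformin treatment start and after 12 weeks of treatment".

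Section 5 starts with the descriptive summary: "Mean and SEM (standard error of mean) of all metabolites will be calculated pre-versus post intervention for the respective sub-samples", which are formed by age and sex. It then tests each metabolite for normality with a Kolmogorov–Smirnov test and splits the analysis in two.

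- **Normal metabolites.** The pre/post differences "shall be analyzed with two-tailed dependent t-tests while correcting for multiple comparisons with Bonferroni correction". In addition, "differences pre-versus post intervention will be further quantified with the calculation of effect sizes by Cohen with pooled standard deviation and 95% confidence intervals".
- **Non-normal metabolites.** "If the hypothesis of normal distribution must be rejected for metabolite concentrations pre-versus post intervention, Wilcoxon tests shall be conducted". On effect size: "For metabolites not showing a normal distribution, effect sizes shall be calculated according to" a cited source. This sentence names no interval.

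The sample is divided further: "For female subjects before versus after menopause, analyses will be conducted separately".

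Section 5 gives no alternative to mean and SEM for metabolites in the non-normal branch.

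**The concern.** The summary does not fit the endpoint or the data that the same section anticipates.

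1. The question is how much each patient changes, but the SEM is computed separately at each visit. It carries the between-patient variation that a paired analysis removes. It also measures the precision of a visit mean, not the spread of patients around it.
2. Mean and SEM are prescribed for all metabolites, so also for those the plan itself would move to a Wilcoxon test. For a right-skewed urinary metabolite, the mean is pulled above the typical patient.
3. An SEM shrinks as the group grows. Section 3.6 expects mainly patients over 50 and slightly more men than women, so sub-samples by age, sex and menopausal status will differ in size. Equal spread will then show as unequal SEMs.
4. The only interval named is attached to a standardised effect size in the normal branch.

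At stake is how well the size of each change can be estimated and reported. The Discussion hopes the results will trigger a randomised trial. Its designers would want the SD of the within-patient change, which Section 4.4 did not have for this study.

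**Working it through.** **Inputs**

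- Testosterone 2.7 ± 0.3 falling to 2.0 ± 0.2 nmol/L (Section 4.4). The article does not say whether ± is SD or SEM; SD is assumed here.
- Per-metabolite alpha 0.001136, which equals 0.05/44; power 80%; n = 7, and around 45 for one-fourth of the effect (Section 4.4).
- Pre/post correlation r: not given. Assumed range 0 to 0.9.
- Degree of skew: not given. Log-normal with log-SD 0.5 to 1.0 is assumed.

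**Step 1. The plan's own figures.** Average SD = sqrt((0.3² + 0.2²)/2) = 0.255, so d = 0.7/0.255 = 2.75. Using this as the paired effect in a two-sided t-test at alpha 0.001136 with 80% power gives n = 7, as stated. One-fourth of it, d = 0.69, gives 41. Taking one-fourth of the change with r = 0.5 instead (0.175/0.265 = 0.66) gives 44. Both are consistent with around 45. This point disputes neither figure, and no SEM from Section 5 enters them.

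**Step 2. Visit SEM against the standard error of the change, n = 45.** sqrt(45) = 6.71.

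- SEM before = 0.3/6.71 = 0.045; SEM after = 0.2/6.71 = 0.030. Neither depends on r.
- SE of change = sqrt(0.3² + 0.2² − 2·r·0.3·0.2)/6.71.
- The two SEMs combined as if independent: sqrt(0.045² + 0.030²) = 0.054.

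| r (assumed) | SE of paired change | 0.054 divided by it |
|---|---|---|
| 0 | 0.054 | 1.00 |
| 0.3 | 0.046 | 1.18 |
| 0.5 | 0.039 | 1.36 |
| 0.7 | 0.032 | 1.68 |
| 0.9 | 0.022 | 2.43 |

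The same pair of SEMs fits every row, so the precision of the change cannot be recovered from them without r.

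**Step 3. SEM as a measure of spread.** At n = 45 the SEM is the SD divided by 6.7. For illustration, if 45 patients split 30 and 15 with equal SD, the SEM in the smaller group is sqrt(30/15) = 1.41 times that in the larger.

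**Step 4. Skewed metabolites.** For a log-normal variable, mean/median = exp(s²/2). This is 1.13 at s = 0.5, 1.38 at s = 0.8 and 1.65 at s = 1.0, so the mean lies 13% to 65% above the median.

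**Step 5. Where intervals are named.** In the normal branch, 95% confidence intervals appear in the sentence on Cohen's effect size. In the non-normal branch, the article names an effect size and no interval.

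**The case against.** The strongest reply is that the SEMs are only descriptive. Section 5 says that they will be calculated. It mentions no plots or error bars and does not present them as the precision of the change, which is judged by paired t-tests or Wilcoxon tests. This stands, and it sets the weight of the point.

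A reader might infer that the reported SEMs will contradict the paired tests. The article does not support that. The ratios in the table arise only if someone combines two visit SEMs as independent and ignores the paired test reported beside them, and they rest on an assumed r.

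A reader might also infer that the size of a change could not be read at all. That is not so. The two visit means give the mean change in the metabolite's own units, and normal metabolites get a standardised effect size with an interval. If n is printed, SD = SEM × sqrt(n). Where an exact paired t is reported, the SD of the change follows as mean change × sqrt(n)/t. The Wilcoxon branch has no such route.

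On intervals, the normal-branch sentence could be read as covering the differences themselves as well as the effect sizes. Silence on the non-normal branch, in a condensed article, may be filled by a fuller document that is not shown. That part is therefore weak on its own.

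What the reply does not remove is a choice that is written down: mean and SEM for all metabolites, in a paragraph that treats some of them as non-normal and in a study whose primary endpoint is a paired change.

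**Conclusion.** The point holds as a low-severity weakness in estimation and reporting. The prescribed visit-wise summary measures neither the spread of patients nor the precision of the within-patient change, and it describes skewed metabolites poorly. As written, 95% confidence intervals are tied only to the normal-branch effect sizes.

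On size: with the article's testosterone values read as SDs and n = 45, one fixed pair of SEMs is compatible with a standard error of the change from 0.054 down to 0.022 over r = 0 to 0.9. Under the assumed log-normal range, the mean overstates the median by 13% to 65%. Both ranges rest on assumptions, because the article gives neither a correlation nor a degree of skew. That a visit-wise SEM cannot give the precision of a paired change does not depend on them.

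No p-value, significance threshold or planned sample size changes.

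**What to change.** In Section 5:

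- Replace SEM at each visit by SD, or by median and quartiles for skewed metabolites, with n shown for each sub-sample.
- For every metabolite, report the paired change with a 95% confidence interval. Suitable forms are the post/pre ratio of geometric means from log differences, or the Hodges-Lehmann paired shift for the Wilcoxon branch. One scale across all metabolites makes comparison easier.
- Report the SD of the within-patient change (on the log scale if ratios are used).

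The paired tests and the Bonferroni correction can stay as they are. The cost is a few sentences and some extra table columns, with no new data. The visit-wise spread will look wider than SEMs would, because it then shows variation between patients.
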